# Evaluating the effectiveness of the Play Active policy intervention and implementation support in early childhood education and care: a pragmatic cluster randomised trial protocol

**DOI:** 10.1186/s12889-022-12729-5

**Published:** 2022-02-14

**Keywords:** Physical activity, Screen time, Sedentary, Childhood, Childcare, Intervention, Policy, Implementation

## Abstract

**Background:**

Daily physical activity is critical during the early years of life for facilitating children’s health and development. A large proportion of preschool children do not achieve the recommended 3 h of daily physical activity. Early childhood education and care (ECEC) services are a key setting to intervene to increase physical activity. There is a significant need for ECEC specific physical activity policy, including clearer guidelines on the amount of physical activity children should do during care, and strategies for implementation of these guidelines.

**Methods:**

This study is a pragmatic cluster randomised trial to evaluate the effectiveness of the Play Active physical activity policy intervention to improve early childhood education and care educator’s physical activity-related practices. The central component of Play Active is an evidence-informed physical activity policy template which includes 25 practices to support nine age-specific recommendations on the amount of physical activity and sedentary time, including screen time, young children should do while in care. There are six implementation support strategies to facilitate physical activity policy implementation: (i) personalise policy (services select at least five of the 25 practices to focus on initially); (ii) policy review and approval; (iii) a resource guide; (iv) a brief assessment tool for monitoring children’s energetic play; (v) professional development; and (vi) Project Officer implementation support (phone calls). A total of 60 early childhood education and care services will be recruited from metropolitan Perth, Western Australia. After baseline assessment, services will be randomly allocated to either intervention or wait-listed comparison conditions. Primary (educator-reported frequency and amount of daily time provided for children’s physical activity, sedentary and screen time) and secondary (educator physical activity-related practices, self-efficacy, motivation, attitudes and beliefs, social support, and supportive physical environment) outcomes will be assessed at baseline and post-intervention, after intervention services have had a minimum 3 months of policy implementation within their service.

**Discussion:**

The Play Active trial will rigorously evaluate a novel physical activity policy intervention with implementation support that promotes positive physical activity behaviours in educators and children attending ECEC. If effective, the program could be adapted, scaled-up and delivered in ECEC services nationally.

**Trial registration:**

Australian New Zealand Clinical Trials Registry ACTRN12620001206910 (date of registration 13/11/2020).

**Supplementary Information:**

The online version contains supplementary material available at 10.1186/s12889-022-12729-5.

## Background

Daily physical activity is critical during the early years of life [1]. Regular physical activity provides children with health and developmental benefits, including a healthy weight, improved bone health, cardiovascular fitness, and enhanced cognitive, emotional and psychosocial development [2]. A large proportion of preschool children do not achieve the recommended 3 h of daily physical activity [3–5]. A key setting of influence for young children’s physical activity is centre-based childcare services, referred to as early childhood education and care (ECEC) services in Australia. These include preschools, long-day care services and kindergartens that provide educational and developmental activities for children prior to the commencement of compulsory schooling [6]. Research shows that ECEC services have a larger influence on variations in levels of young children’s (2–5 years) physical activity than socio-demographic factors [7]. Yet systematic reviews of intervention studies implementing physical activity policies, practices or programmes within ECEC services indicate little evidence of benefit on young children’s physical activity [6]. This is due to lack of efficacy that the intervention improves children’s physical activity, lack of implementation supports (e.g., management support, external resources, training), implementation barriers (e.g., lack of support, negative attitudes, poor self-efficacy, lack of physical space), the intervention not being conducive to real-word conditions (loss of effect size) and the insufficient use of evidence-based behaviour change frameworks [6].

There is a need for multilevel and multicomponent implementation interventions in ECEC settings that are underpinned by comprehensive evidence-based behaviour change frameworks [8]. Social-ecological models of behaviour change integrate many behaviour change theories [9]. Four core concepts underpin social-ecological models: 1) multiple levels of factors influence health behaviours from individual factors through to a wide range of social and environmental factors; 2) complex and dynamic interactions of multilevel factors work together to influence behaviour; 3) social-ecological models are most useful when tailored to specific health behaviours; and 4) interventions systematically targeting multilevel factors of influence are most effective in changing and sustaining behaviours at the population level [10–12]. Physical activity intervention research based upon a social-ecological framework may lead to more effective implementation and enable successful scale up [10].

Consistent with socio-ecological models, implementation of physical activity policy is important for changing the physical activity practices of educators to positively impact children’s physical activity levels in care and over the longer term. In ECEC settings, the policy environment can influence children’s physical activity in varying ways. This can be indirectly through having a written ‘health and safety’ policy that protects children from extreme weather conditions when playing outdoors (i.e., sun protection), or a specific written physical activity policy [13], through to regulatory requirements and standards requiring services to have and implement a physical activity policy [14, 15]. However, only half of all Australian, New Zealand, Canadian and US services have a written physical activity policy [16–19] with considerable within country variation [16, 20]. Interventions to develop and effectively implement written physical activity policies are needed in ECEC [13, 21].

In addition to ECEC services having policies with clear guidance on the amount and type of physical activity children should do whilst attending care, strategies to support the implementation of physical activity policy-related practices are also needed. A number of key physical activity practices have been identified as necessary for successful policy implementation, including practices related to management, supervisors and educators [22]; the ECEC physical environment; communicating with families; and accreditation, monitoring and review [13]. As educators are recognised as gatekeepers of children’s behaviour in ECEC, improving educator physical activity practices is an important component of effective physical activity policy implementation [23].

While educators agree on the importance of physical activity for children’s health and development, there appears to be low awareness of the amount, type and nature of physical activity that is needed for it to be beneficial for children’s health and wellbeing [13]. Moreover, most Australian educators do not receive professional development and training in relation to physical activity [13]. Pilot studies have shown outdoor nature-based play and fundamental movement skill professional development programs tailored to the ECEC setting to be effective in improving educators’ self-efficacy to engage children to be physically active [24]. Further research is needed to identify the most effective content and means of delivering quality professional development and training for educators, to provide them with the necessary skills and tools for promoting the physical activity levels of children in their care [8].

To address these needs, the Play Active program was developed. Play Active is a physical activity policy intervention with accompanying implementation support strategies, with the overarching goal to increase physical activity levels in young children (< 5 years) attending ECEC. The central component of Play Active is an evidence-informed physical activity policy template containing 25 practices to support nine key age-specific recommendations and two key statements which provide clear guidance on the amount of physical activity and sedentary time, including screen time, young children should do while attending ECEC [13]. There are six implementation support strategies to facilitate physical activity policy implementation within ECEC services:(i)Personalise policy: services select at least five from 25 practices within the physical activity policy template to focus on initially [13].(ii)Policy review and approval: services submit draft policy to a Play Active Project Officer; two Project Officers subsequently review the policy against minimum criteria and approve or provide tailored feedback to reach approval.(iii)Resource guide: with practical tips and activity suggestions, resources are mapped to the 25 practices within the policy.(iv)Brief assessment tool: for monitoring young children’s physical activity levels, provided within the resource guide.(v)Professional development: training on fundamental movement skills and active play-based learning, provided by Play Active partners.(vi)Project Officer implementation support: including both weekly follow-up (phone and/or email) to complete the policy review and a mid-implementation prompt (phone call) to determine whether policy implementation has commenced.

This paper describes the protocol of a pragmatic cluster randomised trial to evaluate the effectiveness of the Play Active physical activity policy intervention (with implementation support strategies) on increasing the frequency and amount of time each day ECEC educators provide for young children’s physical activity, sedentary and screen time (primary aim). Secondary aims will examine the effects of the intervention on:Educator physical activity practices, specifically increasing modelling of physical activity, programming and planning physical activity, and promoting and encouraging physical activity, and decreasing use of physical activity for managing misbehaviour.Increasing the proportion of ECEC educators who report a positive attitude, feel confident and motivated, feel supported by management and co-workers, and have a supportive physical space for promoting young children’s physical activity.The proportion of ECEC services with staff who take up and complete physical activity-related professional development and training.

The protocol follows the SPIRIT guidelines (Additional file 1) [25].

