## Methods

### Study design and setting

This pragmatic cluster randomised trial design involves 60 ECEC services in Perth metropolitan and Peel regions of Western Australia. The design was selected to maximise the applicability to ECEC services, that is, to test the Play Active physical activity policy intervention and accompanying implementation support strategies with a wide range of ECEC staff (directors and educators), while simultaneously enabling the program to be as close to real world conditions as possible [26]. At the conclusion of baseline data collection, ECEC services will be randomly allocated to either the intervention (physical activity policy template plus six implementation support strategies) or wait-listed comparison groups. Primary and secondary trial outcomes will be assessed for change immediately following the (up to 6 month) intervention period. The trial is registered through the Australian New Zealand Clinical Trials Registry (reference number 12620001206910, registered 13/11/2020). An overview of the study design, schedule for enrolment and study assessments is shown in Table 1.

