**Table 1 Tab1:**
[figure not shown]
Schedule of enrolment, intervention, and assessments for the evaluation of the Play Active policy intervention and implementation support

Primary outcomes: educator-reported frequency and amount of time per day provided for children’s physical activity, sedentary and screen time. Secondary outcomes: educator physical activity practices, self-efficacy, motivation, attitudes and beliefs, social support, supportive physical environment and professional development training. ^1^For services allocated to intervention group only

The setting for this pragmatic trial are ECEC long-day care services, which provide centre-based childcare by professional staff for large groups of young children prior to formal compulsory schooling [27]. In Australia, ECEC long-day care services are mostly privately owned by providers, with the vast majority of providers approved to operate a single service only (81%), requiring enrolment and a daily fee for service [28]. ECEC services are highly regulated; the Australian National Quality Framework for ECEC outlines minimum standards across seven quality areas, including quality area 2.1.3 which states ‘healthy eating and physical activity are promoted and appropriate for each child’ [15]. As of February 2021, the regulating body, the Australian Children’s Education and Care Quality Authority reported there were 557 ECEC long-day care services located in the Perth and Peel metropolitan region of Western Australia. As the National Quality Framework also sets out minimum educator to child ratio requirements for ECEC services, there was an average of 66 approved places for children per service in the study region (range = 13–223 children).

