#### Policy implementation supports

Alongside the physical activity policy template, directors will be provided with six implementation support strategies. The itemised components of each implementation support strategy are detailed in Additional file 2 and summarised below.(i)Personalise policy: ECEC service staff will be encouraged to personalise the physical activity policy template to suit their service and the needs of their attending children and families. Services are asked to *select at least five from 25 practices* to prioritise during initial implementation. To support ECEC services in this, seven high impact and low effort practices, based on previous testing [13] are indicated.(ii)Policy review and approval: Services are asked to submit their draft physical activity policy (based on the template) to Play Active. Two Play Active Project Officers independently review the policy and approve policies that meet minimum criteria. The minimum requirements for physical activity policies to be approved are that it include: two (out of two) key statements; nine (out of nine) recommendations; and at least five (out of 25) practices to prioritise implementing during the trial’s intervention period. After service’s physical activity policies have been approved as meeting the minimum requirements, services will be provided with the remaining implementation support strategies to assist with policy implementation and encouraged to implement the policy over a minimum period of 3 months. Services will be granted a period of up to 2 months for personalising and submitting physical activity policies for approval. After 2 months, any services that do not submit a physical activity policy for review and approval will be provided with all policy implementation supports. Personalisation of the policy and the policy review process is important to enhance policy ownership and implementation of the policy within each service. This process aligns with standard practice in ECEC service’s when initiating and implementing any new policy.(iii)Resource guide: An evidence-informed resource guide (hard copy and digital PDF) with practical tips describing how to implement each of the 25 physical activity practices into daily practice has been developed. The resource guide consists of the following sections: glossary of terms; policy template; benefits of being an accredited Play Active service; and a section covering each of the 25 practices. The 25 practices are consistent with the policy template and outline practical strategies educators can use, an evidence-informed explanation of what it means, and various evidence-based helpful resources for more information. One physical copy of the resource guide is provided to each service as well as an electronic copy.(iv)Brief assessment tool: A brief monitoring tool has been created for educators to monitor children’s physically activity whilst attending ECEC. The Energetic Play Assessment Tool was adapted from a brief instrument developed by Rice and colleagues [30]. For each child, educators record how much of a typical day in the last month was spent energetically playing (e.g., running, jumping, skipping, dancing, riding, climbing and energetic games) indoors and outdoors. There are five response options (very rarely energetic, rarely energetic, sometimes energetic, often energetic, very often energetic) recorded across four parts of the day (arrival to morning tea, morning tea to lunch, lunch to afternoon tea, afternoon tea to departure). Reliability and validity of the tool is currently being assessed. The tool is included as part of the resource guide.(v)Professional development: Training to upskill educators in providing more physical activity opportunities for children in their care, including specific skills on developing fundamental movement skills and active play-based learning. The training for educators will be made available by study partners (Nature Play WA and KIDDO). The Nature Play WA training involves five self-paced centre-based e-learning modules with associated resources. Each module has up to 40 segments of content, equates to 3–4 h of training per module and is expected to take at least 6 weeks to be completed. As part of the trial there is a cost of $99 per module per service. The module topics include: the importance of being a playful educator; active and playful outdoor learning environments; using outdoor play to increase physical activity; planning cycles for active outdoor play; and documenting as a process of reflection, intention and communication. The KIDDO professional development training will be provided to services for free as part of the trial and focusses on developing children’s physical literacy (fundamental movement skills). It involves six, 30–60-min online training modules which individual educators complete at their own pace. Module topics cover the importance of physical literacy; what are fundamental movement skills; teaching fundamental movement skills in early childhood; active ECEC environments; physical literacy in ECEC; and promoting motivation in children. The research team has shown in pilot studies that both professional development training options are feasible and effective in improving educators’ self-efficacy to engage children to be physically active in ECEC [24].(vi)Project Officer implementation support: including both weekly follow-up (phone and/or email) to complete the policy review and a mid-implementation prompt (phone call) to determine whether policy implementation has commenced. Service directors will be provided weekly email and phone call reminders to return their policy for review for up to 2 months.

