### Process outcomes

To understand the mechanisms by which policy implementation support strategies did or didn’t work, process evaluation outcomes will be measured post-intervention for intervention service directors and educators [37, 38]. Survey measures will include the reach of the implementation support strategies, the acceptability and appropriateness of the Play Active program (policy and implementation support strategies) and educator feedback on adaptations to improve the program.

Uptake of the implementation support strategies (reach) will be measured using multiple methods. These include project management logs to see if the policy template is returned for review; website data from partners (Nature Play WA and KIDDO) to assess the uptake of professional development by educators as well as self-report items in the educator post-intervention survey. To further assess reach, educators will also be asked whether their service has a physical activity policy and how often they used the resource guide (assessed on a seven-point Likert scale from once (1) to more than once per day (7)). To assess knowledge of the Play Active program, educators will also be asked a series of true/false knowledge questions based on the content of the physical activity policy recommendations (coverage).

Director- and educator-reported satisfaction (acceptability) with the Play Active program, including open ended questions about what they liked most and what could be improved will be collected. The educator post-intervention survey will also include items on the usefulness (appropriateness) of the resource guide and professional development (assessed on a five-point Likert scale from not at all useful (1) to extremely useful (5)), and what they liked most (acceptability) and what could be improved (suggested adaptations).

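### Professional-development uptake is a secondary aim about the intervention's effect, but the only measure described is a post-intervention process measure in intervention services

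*Protocol article*

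**What the plan says.** All references are to the protocol article.

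- **Background, aims paragraph.** The list of secondary aims opens with "Secondary aims will examine the effects of the intervention on", and its last item is "The proportion of ECEC services with staff who take up and complete physical activity-related professional development and training".
- **Table 1 legend.** The secondary outcomes end with "social support, supportive physical environment and professional development training".
- **Study design and setting.** Primary and secondary outcomes are to be assessed for change "immediately following the (up to 6 month) intervention period".
- **Abstract and Secondary outcomes section.** Both describe secondary outcomes (practices, self-efficacy, motivation, attitudes, social support, physical environment). Neither includes professional development, and no item, scale or data source is given for it there.
- **Process outcomes.** This section says that "process evaluation outcomes will be measured post-intervention for intervention service directors and educators". Under reach it names "website data from partners (Nature Play WA and KIDDO) to assess the uptake of professional development by educators", together with self-report items in the educator survey after the intervention.
- **Statistical analysis.** Quantitative process data are to be summarised descriptively.
- **Wait-listed comparison.** These services receive the policy template and the six supports, training included, only once follow-up data have been collected.

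**The concern.** The same quantity is placed in two classes. The aims and the Table 1 legend make it an outcome on which a randomised effect will be shown. The measurement text makes it a process indicator for one arm.

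An effect needs the same quantity from both arms. If the plan is followed as written, the report will hold one percentage from the intervention arm, which a reader could take for an effect because the aim is worded that way.

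The measure is also narrower than the aim. The aim covers any training related to physical activity. The partner website data cover two courses, and those courses are themselves one of the six supports being delivered. In the intervention arm the logs therefore show how far the intervention was taken up. They do not show whether it raised training overall, and they would miss training from anyone else.

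**Working it through.** The plan states no rate, sample size or power for this outcome, so there is no figure to reproduce. The check is whether the described data can supply the stated quantity.

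**1. What the aim requires.** Let p be the proportion of services whose staff take up and complete training, with I for intervention and C for comparison.

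- Between-arm effect at follow-up: p(I, post) − p(C, post).
- Change within an arm: p(post) − p(baseline).
- Difference in change: [p(I, post) − p(I, baseline)] − [p(C, post) − p(C, baseline)].

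**2. What the text describes.**

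| | Baseline | Post-intervention |
|---|---|---|
| Intervention | none described | partner website data and self-report (Process outcomes) |
| Comparison | none described | none described |

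One of the 2 × 2 = 4 cells is filled. The between-arm effect needs two cells in the right-hand column, the change needs two in one row, and the difference in change needs all four. None of the three can be computed.

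**3. Could the comparison cell be set to zero?** Comparison services have no programme access to the partner courses before follow-up, so a rate near zero for those courses would be plausible. The aim is not limited to them. The Background says that most Australian educators receive no training related to physical activity, which leaves some who do. If p(C, post) is taken as zero, the effect is overstated by exactly p(C, post), and the document gives no value for it.

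**4. Which statement governs?** The Participant response and retention section says in general terms that every service takes part in both rounds of data collection. The Process outcomes section restricts these particular measures to intervention directors and educators. The specific statement is the natural one to follow. The same block asks about use of the resource guide, which comparison services do not yet have, so it reads as a set of questions for the intervention arm.

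**The case against.** **Comparison educators may be asked after all.** Both arms receive the follow-up educator survey, and the self-report items sit in that survey. The body of Table 1 is not shown, nor are the rows to which its intervention-only footnote belongs. The survey forms are not shown either, and an article often leaves item-level detail to a fuller document. This part stands: a reader might infer that comparison-arm data will not exist, and the documents do not establish that. They support only the statement that none are described. The conflict between the sections remains whatever the table shows, because the aims and the legend call this a secondary outcome and the measurement text calls it process.

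**A stronger reading concerns the calendar.** The Nature Play WA course has five modules, and each involves 3–4 h of "training per module and is expected to take at least 6 weeks to be completed". A reader might infer that the course cannot be finished in time: 5 × 6 = 30 weeks, against 6 months × 4.348 = 26.1 weeks at most and 3 × 4.348 = 13.0 weeks for the minimum implementation period. The documents do not support this as a reason why the effect cannot be estimated:

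- The 30 weeks assumes that modules are taken strictly one after another and that completion means all five. Neither is stated. The modules are self-paced and priced singly.
- Even in sequence, two modules (2 × 6 = 12 weeks) fit 13.0 weeks and four (4 × 6 = 24 weeks) fit 26.1 weeks.
- The free KIDDO course takes 6 × 0.5 = 3 h to 6 × 1 = 6 h in total and fits every window.
- Starting a module is uptake whatever the calendar, and a long course lowers a completion proportion without making a difference between arms inestimable.

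What remains of it is that completion is undefined: one module, one course or every module would give different proportions.

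**It is only the last-listed secondary aim.** That is fair, and it sets the severity.

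**Conclusion.** The concern holds as an internal inconsistency with one practical consequence. Followed as written, the plan yields a single post-intervention proportion in intervention services, which can estimate neither an effect of the intervention on training nor a change in it.

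Severity is minor. One secondary aim is affected. The primary outcomes, the sample size and the primary model are not.

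The conclusion rests on two readings: that the restriction to intervention services in the Process outcomes section applies to the training items listed in that section, and that training from other providers is open to comparison services. If the unseen survey forms put an equivalent item to both arms, the defect reduces to wording, and the sections still need to agree.

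**What to change.** Choose one of two routes.

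**Keep it as a secondary outcome.** Put the same self-report item in the follow-up survey of both arms: any physical activity training started, and any completed, since baseline, from any provider. State what counts as completed and when a service counts as having trained staff. Use this item alone for the between-arm comparison, and keep the partner website data for describing reach in the intervention arm. Because the item asks about the period since baseline and services are randomised, no separate baseline item is needed. Add the measure to the Secondary outcomes section. The cost is one item, with its started and completed parts, in a survey that both arms already receive, and a few lines of text.

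**Or reclassify it.** Make professional development a process outcome, reported descriptively for intervention services, and remove it from the aims worded as effects and from the secondary outcomes in the Table 1 legend. The cost is an edit in two places. This is the only route left if follow-up surveys have already gone to comparison services without the item.
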